#### Plaque reconstruction and analysis

2.6.2

All reconstructed CCTA images will be further evaluated semi automatically using a three-dimensional (3D) contour detection algorithm (Syngo.via Multimodality Workplace, Siemens, Frontier–Coronary Plaque Analysis platform, Siemens, Erlangen, Germany). All coronary vessels with a diameter of at least 2 mm will be assessed using the 19 coronary segments model.

Quantitative evaluation of the atheromatous lesions will include plaque length, vessel volume, lumen volume, plaque volume, and the severity of luminal narrowing. The volumetric measurements will be performed using as reference the proximal and the distal extremities of the plaques, and assessment of plaque composition will include determination of dense calcium and non-calcified plaque components, such as lipid rich and fibrotic tissue.

Qualitative assessment of plaque characteristics will investigate the presence of vulnerability features inside the coronary plaque: PR, LAP, SC, and NRS.

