#### Study definitions

2.6.3

In this study, a significant coronary plaque is defined as a plaque producing at least 50% luminal narrowing. The remodeling index (RI) represents the ratio between the cross-sectional area at the site of maximum stenosis divided by the average of the proximal and distal reference cross-sectional areas, and PR is defined as a remodeling index of 1.1 or greater.^[11]^ Plaques having at least 10% of their content non-calcified, with a CT density of <30 HU will be classified as LAP.^[12]^ SC are defined by a small dense area (>130 HU) surrounded by non-calcified plaque tissue.^[13]^ NRS will be considered present following identification of a non-calcified plaque with a central area of low attenuation in contact with the lumen, and a ring-like higher attenuation tissue, surrounding the central area.^[11,14]^

Cross-sectional plaque eccentricity will be assessed according to the location of the circulant lumen in a transverse section at the level of maximum stenosis. The cross-sectional eccentricity (CE) index will be calculated as follows: (maximum wall thickness – minimum wall thickness)/maximum wall thickness. Eccentric lesions will be defined as having a CE index of 0.3 or greater, whereas concentric lesions will be defined as having a CE index of <0.3. Longitudinal plaque eccentricity, defined as stenosis with an abrupt narrowing of the proximal or distal edge, will be assessed according to the location of maximum stenosis in a longitudinal section. The longitudinal eccentricity (LE) index will be calculated as the ratio of distance between the proximal end of the lesion and the place of maximum stenosis to the lesion length.^[15]^ Lesions with an LE index of ≤0.4 will be classified as descendent; lesions with an LE index of ≥0.6 will be classified as ascendant; and intermediate lesions with an LE index between 0.4 and 0.6 will be classified as non-eccentric plaques.

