### Outcomes

2.8

The primary outcome of the study is represented by the rate of MACE during follow-up. Secondary outcome refers to coronary plaque vulnerability associated to plaque eccentricity, based on the number of vulnerability markers in eccentric versus concentric plaques.

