### Statistical analysis

2.11

Statistical analysis will be performed using Graph Pad InStat 3.10 software (GraphPad Software, San Diego, CA) at the level of significance 5%. All data will be checked for normality. Continuous variables with normal distribution will be presented as mean ± standard deviation and will be compared using *t* test. Non-normally distributed variables will be analyzed using the Mann–Whitney *U* test. Categorical variables will be expressed in numbers and percentages and will be compared using the Fisher exact test.

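### The marker-count comparison of eccentric and concentric plaques is unadjusted, so it cannot by itself show that eccentricity adds information beyond plaque size

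*Protocol article*

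**What the plan says.** Section 2.8 bases the secondary outcome on marker counts, compared "based on the number of vulnerability markers in eccentric versus concentric plaques". The four markers are positive remodeling (PR), low-attenuation plaque (LAP), spotty calcification (SC) and napkin-ring sign (NRS).

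Section 2.11 gives three methods, all of them two-group tests without covariates. Measurements that look normal get a t test, and categories get Fisher's exact test. For a skewed measure such as a marker count, the sentence most likely to apply is this: "Non-normally distributed variables will be analyzed using the Mann–Whitney *U* test".

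The article mentions no regression, stratification or covariate anywhere.

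The candidate covariates are collected. In section 2.6.2 the quantitative evaluation "will include plaque length, vessel volume, lumen volume, plaque volume, and the severity of luminal narrowing". The same section also covers calcified content: "assessment of plaque composition will include determination of dense calcium and non-calcified plaque components".

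The wording of the aim varies. Section 1.2 asks for an association between eccentricity and vulnerability. Section 2.1 wants to validate eccentricity as a new CCTA marker of vulnerability, and section 3 hypothesizes that lesion geometry has an impact on vulnerability.

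**The concern.** The study is not randomized, and its exposure is a property of the plaque. Eccentric and concentric plaques may differ in size, severity or composition as well as shape. If such a feature is linked both to the eccentricity index and to the markers, marker counts will differ between the groups even when geometry plays no part.

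What is at stake is the interpretation of a positive result. Plaque size is already available from the same scan, so a marker that only restates it is not new. An unadjusted test cannot tell the two explanations apart.

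This is a plaque-level matter. It is separate from patient-level confounding of MACE and from several plaques coming from one patient.

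**Working it through.** **The plan's own figure.** None is given for the secondary outcome. The only power statement (section 2.10) concerns MACE. It reproduces approximately: 90% versus 95.4% event-free at 90% power needs 486 per group, and 500 per group gives 90.8% power. It has no bearing on this point.

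**Step 1: which features are linked to what, by the definitions in section 2.6.3.**
- Cross-sectional eccentricity: CE = (max − min)/max wall thickness at maximum stenosis; eccentric if CE ≥ 0.3.
- PR: remodeling index RI = cross-sectional area at maximum stenosis / mean reference area; positive if RI ≥ 1.1.
- LAP, SC and NRS all refer to non-calcified tissue. For example, "NRS will be considered present following identification of a non-calcified plaque with a central area of low attenuation".

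| Feature | Linked by definition to CE? | Linked by definition to markers? |
|---|---|---|
| Plaque size (wall thickness) | Yes, if one wall thickens more than the other | Yes, through PR |
| Calcified content | No | Yes, through LAP, SC and NRS |
| Stenosis severity | No | No |

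Confounding needs both links. Only size can have both by definition. For the other two features, any missing link would be empirical.

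**Step 2: the size link in numbers.** Assumed dimensions: circular vessel, lumen 1.5 mm, reference diameter 3.0 mm, area read as vessel area. Then RI = ((1.5 + max + min)/3.0)².

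| Min wall (mm) | Max wall (mm) | CE | RI |
|---|---|---|---|
| 0.5 | 0.65 | 0.15/0.65 = 0.23 (concentric) | (2.65/3.0)² = 0.78 (PR negative) |
| 0.5 | 1.5 | 1.0/1.5 = 0.67 (eccentric) | (3.5/3.0)² = 1.36 (PR positive) |
| 1.0 | 1.3 | 0.3/1.3 = 0.23 (concentric) | (3.8/3.0)² = 1.60 (PR positive) |

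Row 2 against row 1: one-sided thickening moves both the exposure and a marker. Row 3 against row 1: proportional thickening moves the marker but leaves CE unchanged. The link between size and CE is therefore possible but not automatic.

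**Step 3: what such links could do.** The document gives no correlations, odds ratios or marker prevalences, so every input below is assumed. Both simulations have four markers, no true effect of eccentricity, one plaque per patient, 1,000 runs per setting and a nominal 5% level.

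*Size and calcified content together.* 1,000 plaques, about half of them eccentric, marker probability about 30% at average covariates. Each covariate has an odds ratio of the same strength per SD on eccentricity and on each marker; calcified content acts in the opposite direction to size.

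| Odds ratio per SD | Mann–Whitney, both links | Adjusted regression, both links | Mann–Whitney, marker link only |
|---|---|---|---|
| 1.0 (no link) | 4.9% | 4.8% | 5.8% |
| 1.25 | 25.8% | 4.9% | 5.5% |
| 1.5 | 95.8% | 5.7% | 5.0% |
| 2.0 | 100% | 4.7% | 5.9% |

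*Size alone.* 70% of plaques eccentric, marker prevalence 20%, 1,500 plaques. Unadjusted Mann–Whitney rejection rates:

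| Correlation of CE with log size | Marker odds ratio 1.3 per SD | Marker odds ratio 1.6 per SD |
|---|---|---|
| 0.1 | 9.6% | 16.6% |
| 0.2 | 23.1% | 51.0% |
| 0.3 | 41.9% | 83.2% |

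With 1,000 plaques the unadjusted range is 7.0% to 70.2%. Adjusting for size gives 4.2% to 6.5%.

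Modest links suffice to distort the unadjusted test. Without a link to eccentricity there is no distortion.

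**The case against.** The strongest reply is that the secondary objective asks only for an association, and an unadjusted comparison answers that. Whether eccentricity adds information beyond plaque size is a different question. This stands for section 1.2. It does not cover the aim of validating a new marker in section 2.1, which is where the weakness lies.

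Second, adjustment may remove part of the outcome. PR is a ratio of areas and shares content with plaque size. Section 3 lists non-calcified and lipid-rich plaque among the vulnerability features expected to go with geometry. This also stands, and it is why the adjusted estimate should accompany the unadjusted one and not replace it.

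Third, this is a condensed article, section 2.11 assigns no particular test to this outcome, and an analysis plan may add covariates. That limits the weight of the point. Still, the methods actually named are all unadjusted.

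A reader might infer that size, severity and calcification all drive both the eccentricity index and the markers. The definitions do not support that: calcified content is tied only to the markers, and stenosis severity to neither. A reader might also infer that a mainly calcified plaque must score near zero on LAP, SC and NRS. That is too strong, since SC requires a dense area and LAP asks for only 10% low-density non-calcified content.

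**Conclusion.** The point holds as a possible confounding problem in a stated method. The comparison is covered only by unadjusted tests, while measured plaque features may confound it, plaque size most clearly. An observed difference would establish an association. It would not establish that eccentricity is a marker beyond size.

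The size and even the presence of bias cannot be derived from the document. The simulated error rates rest wholly on assumed inputs, and it would be wrong to read them as the error rate this study will have. The adjustment is a cheap improvement to a secondary analysis, graded as a point to consider.

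**What to change.** Keep the unadjusted comparison. Add a prespecified plaque-level regression of marker count, and of each marker separately, on eccentricity. Adjust for plaque volume or length and for percent luminal narrowing, and report estimates with 95% confidence intervals beside the unadjusted result. Show a further model with the dense-calcium share as a sensitivity analysis only, because composition is partly the outcome. State in advance that any claim of eccentricity as a new marker rests on the adjusted estimate.

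Cost: wording in the analysis plan, a little more analysis work, and software that can fit the model. No new data are needed. The main downside is possible over-adjustment, notably for PR, which is the reason for reporting both estimates.

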### Participation timeline

2.9

Screening (Day 0)

Obtain and document consent from participant on study consent form.Verify inclusion/exclusion criteria.Imaging: 128-multislice CT angiography scanning and basic plaque assessment—presence of coronary plaque and degree of luminal narrowing.

Baseline (day 0):

-Obtain demographic information, medical history, medication history, alcohol, and tobacco use history.-Record results of physical examinations and 12-lead ECG.-Collect blood specimens.-Imaging: image post-processing for complex plaque assessment—plaque morphology, composition, and geometry

Visit 1 (month 6):

-Record results of physical examinations, 12-lead ECG, and medical history.-MACE assessment.

Visit 2 (month 12):

-Record results of physical examinations, 12-lead ECG, and medical history.-MACE assessment.

Visit 3 (month 18):

-Record results of physical examinations, 12-lead ECG, and medical history.-MACE assessment.

Final study visit (month 24):

-Record results of physical examinations, 12-lead ECG, and medical history.-Repeat CCTA and plaque assessment.-End-point evaluation.

Figure 1 illustrates the GEOMETRY diagram with the flowchart that will be used in the study.

**Figure 1 F1:**
[figure not shown]
Flowchart diagram of GEOMETRY study.

### Sample size

2.10

The study will include 1000 subjects with suspected CAD who are referred to CCTA by the attending physician and in which presence of at least 1 coronary plaque is confirmed by CCTA. After analysis of coronary plaques eccentricity index, patients will be distributed in 2 groups according to the presence or absence of significant eccentric lesions in coronary arteries.

Sample size calculation was performed using the StatMate 2.0 software (GraphPad Software, San Diego, CA). For sample calculation, the proportion of event-free population was estimated at 90%. According to this calculation, a sample size of 500 patients in each subgroup has a 90% power to detect an increase in MACE-free rates proportion of 0.054, with a significance level (alpha) of 0.05 (two-tailed). Therefore, the total sample size was established at 1000 patients.

### Statistical analysis

2.11

Statistical analysis will be performed using Graph Pad InStat 3.10 software (GraphPad Software, San Diego, CA) at the level of significance 5%. All data will be checked for normality. Continuous variables with normal distribution will be presented as mean ± standard deviation and will be compared using *t* test. Non-normally distributed variables will be analyzed using the Mann–Whitney *U* test. Categorical variables will be expressed in numbers and percentages and will be compared using the Fisher exact test.

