### Study design

2.1

GEOMETRY is a prospective, non-randomized, cohort, single-center study to investigate the relationship between plaque eccentricity, plaque vulnerability, and the risk for MACE in order to validate plaque eccentricity as a new CCTA marker of coronary plaque vulnerability.

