### Study population

2.3

GEOMETRY will be a non-randomized, observational, single-center study including patients with chest pain and pre-test probability of coronary artery disease between 15% and 85%, referred for CCTA (according to the recommendation of the guidelines of the European Society of Cardiology).^[10]^

Inclusion criteria:

Patients with suspected coronary artery disease (CAD) and pre-test probability of CAD between 15% and 85%, who undergo CCTA, and in whom CCTA will identify presence of at least 1 significant coronary plaque (producing a luminal narrowing of at least 50%).Ability to provide informed consent.Age over 18 years.

Exclusion criteria:

Patients with pre-test probability of CAD >85% or <15%.Electrocardiographic evidence of ST-segment elevation acute myocardial infarction.Presence of pre-existing CAD including prior myocardial infarction.History of coronary artery revascularization (by percutaneous coronary intervention, stent, or bypass graft surgery).Atrial fibrillation or other irregular rhythm.Unwillingness or incapacity to provide informed consent.Allergy to iodine contrast media.Inability to tolerate beta-blocker medication.Renal insufficiency (serum creatinine values higher than 1.5 mg/dL) or renal failure requiring dialysis.Pregnant women or lactation.Active malignancy or malignancy within the last 5 years prior to enrolment.Conditions associated with an estimated life expectancy of under 2 years.Coronary calcium score >1000.

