### Study groups

2.5

One thousand patients who meet the selection criteria will be included in the trial and will be divided into 2 groups, namely patients in whom screening CCTA analysis identifies only non-eccentric coronary plaque (group 1) and patients in whom CCTA analysis reveals the presence of at least 1 eccentric significant coronary plaque producing a significant luminal narrowing (group 2).

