### Study procedures and outcome assessment

2.6

In all patients clinical data including sex, age, comorbidities, history of coronary artery disease, stroke, peripheral arterial disease, diabetes, smoking status, as well as clinical status and laboratory tests (creatinine, total cholesterol, low-density lipoprotein [LDL]-cholesterol, triglycerides) will be recorded. All patients will undergo CCTA scanning of the coronary arteries at screening and will be enrolled in the study if CCTA reveals the presence of at least 1 obstructive coronary plaque in any coronary artery. In randomized patients, CCTA scanning will be followed by complex image postprocessing for assessment of plaque composition, morphology, and geometry, using available research software for plaque reconstruction and analysis.

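### The MACE comparison, read naturally, is an unadjusted Fisher test on a grouping that rises with plaque number, so it can show an association when eccentricity is irrelevant

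*Protocol article*

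**What the plan says.** All references are to the protocol article.

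- **Design and aim (2.1).** "GEOMETRY is a prospective, non-randomized, cohort, single-center study to investigate the relationship between plaque eccentricity, plaque vulnerability, and the risk for MACE", and this is done "in order to validate plaque eccentricity as a new CCTA marker of coronary plaque vulnerability".
- **Entry (2.3).** A patient needs at least one plaque that narrows the lumen by 50% or more. There is no upper limit on the number of such plaques.
- **Exposure (2.5).** Group 1 holds patients whose plaques are all non-eccentric. Group 2 is defined by "the presence of at least 1 eccentric significant coronary plaque producing a significant luminal narrowing (group 2").
- **Outcome and sample size (2.8, 2.10).** The primary outcome is the MACE rate during follow-up. The sample size compares two MACE-free proportions, with 500 patients per group.
- **Analysis (2.11).** Three tests are named: the t test, the Mann-Whitney U test and the Fisher exact test. The sentence that covers MACE is "Categorical variables will be expressed in numbers and percentages and will be compared using the Fisher exact test". No regression, stratification or matching is named.
- **Data recorded (2.6, 2.6.2).** "In all patients clinical data including sex, age, comorbidities, history of coronary artery disease, stroke, peripheral arterial disease, diabetes, smoking status" are recorded, as are LDL-cholesterol, plaque volume and degree of narrowing. None of these has a stated role in the comparison of the groups.

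**The concern.** There are two problems, and they act together.

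First, the groups are not randomised, so a crude difference in MACE carries any difference in risk profile or disease extent between them.

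Second, the grouping rule itself creates such a difference. It is an "any of k" rule: each further significant plaque is another chance to be placed in group 2. Group 2 will therefore tend to hold patients with more lesions, even if eccentricity has no bearing on prognosis. If patients with more lesions have more events, the bias favours the study hypothesis.

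At stake is the main conclusion. A significant Fisher test could be read as validation of eccentricity when it reflects the number of plaques.

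**Working it through.** **1. The plan's own figure.** Inputs from 2.10: MACE-free 0.90 vs 0.954, 500 per group, two-sided alpha 0.05. With mean proportion 0.927:

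- z = [0.054 × √500 − 1.96 × √(2 × 0.927 × 0.073)] / √(0.90 × 0.10 + 0.954 × 0.046)
- = (1.207 − 0.721) / 0.366 = 1.33, so power is 0.908

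Simulated power of the Fisher test is 0.897. The stated 90% reproduces on this reading, and the arithmetic is not the issue. It does show that the planned comparison is of two crude proportions.

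**2. Plaque number and group.** Let k be the number of significant plaques and e the chance that any one is eccentric (assumed). If plaques within a patient are independent, P(group 2 | k) = 1 − (1 − e)^k. At e = 0.4:

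- k = 1: 0.40
- k = 2: 1 − 0.6² = 0.64
- k = 3: 1 − 0.6³ = 0.784

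With k = 1/2/3 in 50/30/20% of patients (assumed), the mean plaque number is 1.43 in group 1 and 1.92 in group 2. The rise with k holds for any e strictly between 0 and 1. Correlation between plaques in the same patient weakens it.

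**3. Expected MACE when eccentricity is irrelevant.** Base case, all assumed: k in 50/30/20%, MACE 6/10/18% for k = 1/2/3, e = 0.5, independent plaques. P(group 2 | k) is 0.50, 0.75 and 0.875.

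- Share in group 2: 0.5 × 0.50 + 0.3 × 0.75 + 0.2 × 0.875 = 0.65
- MACE in group 2: (0.25 × 0.06 + 0.225 × 0.10 + 0.175 × 0.18) / 0.65 = 0.069 / 0.65 = 10.6%
- MACE in group 1: (0.25 × 0.06 + 0.075 × 0.10 + 0.025 × 0.18) / 0.35 = 0.027 / 0.35 = 7.7%

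The spurious gap is 2.9 points, against a planned difference of 5.4 points.

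**4. How often the nominal 5% test rejects.** Simulated trials of 1000 patients with no effect of eccentricity and a two-sided Fisher test. None of the varied inputs is in the article.

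| Assumptions | Fisher rejects |
|---|---|
| No risk gradient by plaque number | about 3–5% |
| Base case, but e = 0.9 | about 6–7% |
| MACE 8/10/12% | 6–8% |
| Risk ratio 1.3 per extra plaque | 7–11% |
| Base case, within-patient correlation 0.5 | about 9–10% |
| Base case, but 80/15/5% with 1/2/3 plaques | 10–12% |
| MACE 7/10/14% | 10–14% |
| Base case, within-patient correlation 0.3 | about 15% |
| Risk ratio 1.5 per extra plaque | 15–19% |
| Base case | about 30% (29–34% across separate runs) |
| Risk ratio 2.0 per extra plaque | 39–48% |

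**5. Does accounting for plaque number remove it?** A Cochran-Mantel-Haenszel test stratified by plaque number was run on the same kind of data. At e = 0.4 it rejected in 5.6% of trials at a risk ratio of 1.5 per plaque, and in 3.3% at 2.0. In the base case and its variants it stayed at about 4–6%.

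**6. Room for an adjusted model.** The planning rates imply 500 × 0.046 + 500 × 0.10 = 73 events, or 500 × 0.10 + 500 × 0.154 = 127 if the second group is worse than 90%. Eight parameters give 73/8 ≈ 9 to 127/8 ≈ 16 events each. Adding the four vulnerability markers gives 12 parameters and 73/12 ≈ 6 at the lower count. These counts assume a 500:500 split, which the grouping rule does not guarantee.

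**The case against.** **Section 2.11 never mentions MACE or a primary analysis.** This stands as a limit. Fisher as the primary test is a reading, not a statement in the article. It is still the natural reading, because Fisher is the only test named for categorical data and the sample size compares two proportions.

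**A condensed article may leave covariate models to a fuller document.** This stands in part. A reader might infer that no adjusted analysis exists anywhere, and the article does not support that. The point does not rest on a missing covariate list, however. The article fixes an exposure rule, a wholly univariable set of tests and an aim of validation, and these do not fit together.

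**The risk gradient is not in the article.** This stands. A reader might take it as given that more lesions mean more MACE, but no section says so or gives a figure. Without a gradient the test keeps its nominal level.

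**The inflation may be small.** This stands too. A reader might infer that the false-positive rate is far above 5%. That holds only for a steep gradient with largely independent plaques; correlated plaques, mostly single-plaque patients or a high prevalence of eccentricity bring it down to about 6–15%.

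**The primary objective in 1.2 is only to evaluate an association, which a crude comparison does estimate.** That is true of the objective. It does not answer the aim in 2.1, which is to validate a marker.

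**Conclusion.** The point holds in conditional form. That group 2 membership rises with plaque number follows from the definition in 2.5, unless plaques within a patient are all alike. That the Fisher test can then reject with eccentricity irrelevant needs one further assumption, that MACE risk rises with plaque number.

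The size cannot be fixed from the article. The supportable range for a nominal 5% test runs from about 5%, through about 6–15% in milder settings, to about 30% or more in steep ones. Stratification by plaque number removes this part of the problem.

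Plaque number is also only one possible confounder. Whatever its gradient, a crude difference in a non-randomised cohort cannot by itself support the claim that eccentricity is a validated marker. The change is worth making before the analysis, because most of the data it needs are already planned.

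**What to change.** In 2.11, make the primary MACE analysis a prespecified adjusted comparison on the study's own eccentricity grouping, which keeps both the cross-sectional and the longitudinal index.

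- **Model.** Use logistic regression, or Cox regression if event dates are recorded; the timeline in 2.9 mentions only MACE assessment at visits. At minimum, use a Cochran-Mantel-Haenszel test stratified by number of significant plaques.
- **Covariates.** Number of significant plaques or total plaque volume, maximum stenosis severity, age, sex, diabetes, smoking and LDL-cholesterol. With eccentricity this is eight parameters if each covariate takes one.
- **Fisher test.** Keep it as descriptive.
- **Incremental value.** Treat the gain over positive remodeling, low-attenuation plaque, spotty calcification and napkin-ring sign as secondary. A count of these markers instead of four terms limits the parameters. State that they may lie on the pathway hypothesised in the Discussion, so adjusting for them may remove part of the effect.
- **Sensitivity analysis.** Define exposure on one index lesion per patient, such as the most severe stenosis.

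**Cost.** Analysis-plan wording, a little more analysis work, software that fits regression models, and some loss of precision. The clinical and burden covariates are already recorded, and significant plaques can be counted from the baseline CCTA.
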